## Abstract

**Background:**

Low back pain persisting for longer than 3 months is a common and costly condition for which many current treatments have low-moderate success rates at best. Exercise is among the more successful treatments for this condition, however, the type and dosage of exercise that elicits the best results is not clearly defined. Tai chi is a gentle form of low intensity exercise that uses controlled movements in combination with relaxation techniques and is currently used as a safe form of exercise for people suffering from other chronic pain conditions such as arthritis. To date, there has been no scientific evaluation of tai chi as an intervention for people with back pain. Thus the aim of this study will be to examine the effects of a tai chi exercise program on pain and disability in people with long-term low back pain.

**Methods and design:**

The study will recruit 160 healthy individuals from the community setting to be randomised to either a tai chi intervention group or a wait-list control group. Individuals in the tai chi group will attend 2 tai chi sessions (40 minutes)/week for 8 weeks followed by 1 tai chi session/week for 2 weeks. The wait-list control will continue their usual health care practices and have the opportunity to participate in the tai chi program once they have completed the follow-up assessments. The primary outcome will be bothersomeness of back symptoms measured with a 0–10 numerical rating scale. Secondary outcomes include, self-reports of pain-related disability, health-related quality of life and global perceived effect of treatment. Statistical analysis of primary and secondary outcomes will be based on the intention to treat principle. Linear mixed models will be used to test for the effect of treatment on outcome at 10 weeks follow up. This trial has received ethics approval from The University of Sydney Human Research Ethics Committee. HREC Approval No.10452

**Discussion:**

This study will be the first trial in this area and the information on its effectiveness will allow patients, clinicians and treatment funders to make informed choices regarding this treatment.

**Trial Registration:**

This trial has been registered with Australian New Zealand Clinical Trials Registry. **ACTRN12608000270314**

## Background

The lifetime prevalence of low back pain (at least one episode of LBP in a lifetime) in developed countries is reported to be up to 85% [1]. A significant number of these patients develop chronic/long-term low back pain, defined as pain persisting for more than 3 months [2,3]. Additional to their pain these patients' health problems typically include reduced physical function and psychological distress [4]. In Australia, it has been reported that one in ten Australians suffer from long-term low back pain [5] and it was announced in 2004 as the most prevalent and single most costly musculoskeletal disorder [6]. These data are consistent with that of other industrialized countries worldwide. In the USA, spinal disorders are the most common cause of activity limitation in people under 45 and account for 57.1% of all musculoskeletal impairments in people up to 65 [7]. Similarly in the UK and Sweden, low back pain was estimated to be the largest single cause of work absence [8].

There are a multitude of treatments used in clinical practice to treat low back pain, with little consensus amongst clinicians as to which is the best approach. A recent review of commonly used therapies for chronic low back pain showed that psychological interventions (including cognitive-behavioral therapy and progressive relaxation), interdisciplinary rehabilitation, spinal manipulation, and exercise therapy are all moderately effective compared with placebo or sham therapies [9]. Exercise therapy is relatively inexpensive, easily accessible and widely used in clinical practice to promote an active approach to pain management. However, exercise therapy encompasses a heterogeneous group of interventions [10-12] that vary in type, frequency and duration. [13-16]. While the most effective approach remains uncertain, a list of exercise therapy components associated with best outcome was generated via a meta-regression analysis conducted as part of a Cochrane review in 2005. Several of these components, such as supervision, stretching and strengthening are features of, or can be easily incorporated into, tai chi programs [17].

Tai chi is a low-impact form of exercise of low to moderate intensity that originated in China and consists of slow controlled sequential movements combined with deep diaphragmatic breathing. It has been used as part of Traditional Chinese Medicine for many years and has recently become the focus of scientific research exploring its health benefits. To date, the research has shown programs to be safe [18]and improve physical measures such as pain, self-reported disability, physical performance and falls recurrence [19-21]. There have also been positive effects shown for a variety of psychological indicators such as depression, anxiety, relaxation, concentration, and self-efficacy [22-25]. Although, the bulk of this research is of low methodological quality and reports on small samples, the results thus far are promising and tai chi deserves consideration as an option in the management of other chronic conditions.

We propose to conduct the first randomized-controlled trial of tai chi exercise for long-term low back pain. If the program proves beneficial, this will provide a low-cost and safe alternative for health professionals in the management of this health problem.

## Methods and design

### Participants

Individuals will be recruited via community advertisements. Interested individuals will be screened via telephone by one of the investigators to determine eligibility using the inclusion/exclusion criteria listed in Table 1. All participants require a minimum self-reported score of "moderate" pain or "moderate" activity limitation due to pain as determined by items 7 or 8 on the Short Form-36 item (SF-36) Health Survey (version 2). They must have a diagnosis of "non-specific low back pain +/- leg pain" and be appropriate for exercise management of their back pain measured by the telephone screening questionnaire. If the individual scores positive on any of the telephone screening items a clinical exam and/or medical review will be conducted by one of the investigators who is also a registered physiotherapist to rule out any serious spinal pathology or contraindication to exercise. Individuals suspected of having a serious spinal pathology or any contraindication to exercise will be referred to their medical practitioner for review. Once cleared by their medical practitioner they will be reconsidered for inclusion in the trial. Potential participants will be screened over the phone using three standardized forms: an inclusion/exclusion criteria sheet, a Physical Activity Readiness Questionnaire (PAR-Q) [26] and a pathology screening questionnaire. Participants that meet all the inclusion criteria will have the trial explained to them in detail and then be asked to provide consent before being enrolled into the trial.

**Table 1 T1:** Inclusion and exclusion criteria for the TAI CHI study

*Inclusion criteria*	
Age	18 to 70 years
Diagnosis	Non-specific low back pain +/- leg pain.
Pain duration	At least 3 months duration.
Pain qualifier	A score of "moderate" or higher on item 7 or 8 of the SF-36.
Usual health care	Current health care regimen stable for at least 4 weeks and individual agrees not to seek changes to health care regimen during the 10 week trial.
Language	English speaking and English literate.
Residential status	Expects to continue residing in Sydney for study duration.

*Exclusion criteria*	

Pathology	Suspected or confirmed serious spinal pathology (fracture, metastatic, inflammatory or infective diseases of the spine, cauda equina syndrome/widespread neurological disorder).
	Nerve root compromise (2 of strength, reflex or sensation affected for same nerve root)
Past medical procedures	Spinal surgery
Current medical status	Scheduled for major surgery during treatment
Pregnancy	Suspected or confirmed pregnancy
Contraindications	Any of the contraindications to exercise listed on the PAR-Q
Work status	If participant's back pain is compensable, all relevant treatment parties need to agree to Tai Chi treatment.
Language	Unable to speak, read and write English.
Previous tai chi experience	Participation in a tai chi program within the last 6 months.

*Temporary exclusion criteria*	

Current health care	If participant has started a new treatment/intervention for their back symptoms within 4 weeks prior to eligibility assessment, the individual is temporarily excluded from participating in the study. The individual will be advised that once the new course of treatment has either finished or has become part of their regular health care routine for more than 4 weeks, and they are still experiencing low back pain symptoms they can contact the project leaders again to participate in the trial.

#### Data collection location

All volunteers will be recruited from the Sydney region, all outcome assessment and tai chi sessions will be conducted at participating community venues within the Sydney metropolitan area.

### Interventions

#### Tai chi program rationale

Currently, the mechanisms underlying tai chi have not been well established. However, tai chi increases flexibility and improves lower body strength, two components that have been associated with successful exercise programs for long-term low back pain [27]. Furthermore, previous research has consistently shown tai chi to have positive effects on pain, physical function and quality of life in other populations with chronic conditions [16-18]. The 4 main styles of tai chi; Chen, Wu, Yang and Sun all contain the same basic principles of slow, continuous movements combined with deep diaphragmatic breathing and maintenance of an upright posture. Compared to the other styles, Sun is characterized by less knee flexion which results in decreased stepping distance and more follow-up steps. These characteristics were found to place a lesser burden on the knee and ankle joints [20]. The Sun style form we have chosen for this study is one that is currently practised and promoted by arthritis foundations worldwide and is also being recommended in clinical practice. The form has been designed by [name], general practitioner and tai chi master and includes 21 moves and can be viewed on DVD.

#### Tai chi instruction method

Tai chi sessions are typically held in group format. Instruction is both verbal and visual. A systematic approach to teaching tai chi has been developed by [name] [28]; it is known as the *Stepwise Progressive Teaching Method*. This approach is used world-wide by certified instructors in the teaching of Tai Chi for Health Forms; *Tai Chi for Diabetes, Tai Chi for Arthritis, Tai Chi for Back Pain *and *Tai Chi for Beginners 24 forms*. This method promotes breaking down the tai chi form into the individual movements and teaching them separately, starting with the first move and moving on to the next in a sequential manner. This method does not change the purity of the tai chi form in any way but provides a standardized teaching method. Thus, our study will use the *Stepwise Progressive Teaching Method *to ensure repeatability. A detailed description of the approach is attached in the Appendix.

#### Tai chi dosage and class format

Participants in the intervention group will receive 18 × 40 min sessions over a 10 week period; 2 sessions/week for the first 8 weeks, 1 session/week for the remaining 2 weeks. The treatment sessions are designed to become less frequent over time to represent what is available in the community and encourage independence and continuation of tai chi exercise when therapy is complete.

Each tai chi session has a lesson plan for the instructor to follow which is located in the instructor's manual. The lesson plan includes a checklist of the topics each session will focus on. The instructor will use the lesson plan to conduct the tai chi class and check off that each topic has been covered. Each lesson plan is sufficiently descriptive to allow an independent tai chi instructor to replicate the tai chi class. An exercise log will be provided for each participant to record their home tai chi practice. The home log is designed as a motivational tool for each participant to record their home practice goals and achievements for each week. At the beginning of each week, the participant will fill out how much time they intend to practise each day. They then take their diary home and record their actual practice time per day. The home logs will then be used in the class sessions to discuss any barriers that may have arisen in achieving their goals. Each tai chi group has a session attendance sheet that the instructor completes at the beginning of each class.

#### Other interventions

A bi-weekly questionnaire will be sent via email to participants in both treatment and control groups. The questionnaire will collect the health services accessed by the participant in the prior 2 weeks. Examples of health services include physiotherapy, chiropractic, acupuncture, massage and GP visits related to back symptoms. If no response is received within 24 hrs, a second email will be sent as a follow-up. If no response is received within 48 hrs, the participant will be contacted via phone. Participants in both treatment and control groups will be asked not to seek any new treatments for their chronic low back pain and where possible not to change current treatment during the trial intervention period.

#### Safety

If a participant is concerned about his or her condition during the study, they will be referred to discuss the situation with one of the investigators who is a registered physiotherapist. Where appropriate, the physiotherapist will refer the patient to a medical practitioner.

### Objectives

#### Study aim

The primary aim of this project is to establish whether tai chi exercise is more effective than usual care in the management of long-term low back pain. Individuals who have low back pain for at least 3 months will be randomly assigned to either a tai chi exercise group or to a wait-list control group. The tai chi group will participate in a 10 week sun-style tai chi program consisting of 18 × 40-min group sessions led by a certified instructor. The primary study outcome will be change in an individual's self-reported level of "bothersomeness of back symptoms" as measured by an 11pt numerical rating scale. Secondary outcomes will include change in self-reported intensity of pain, physical function, global perceived effect of treatment and health related quality of life measures.

#### Primary Hypotheses

The effect of a 10 week tai chi exercise program and usual health care is greater than that of usual health care alone where effect is measured in terms of bothersomeness of back symptoms, disability and global perceived effect of treatment and quality of life.

### Outcomes

The primary endpoint with respect to the effectiveness of a 10 week tai chi program for long-term low back pain is bothersomeness of back symptoms measured on an 11 point numerical rating scale. This scale is being more widely used in back pain research and has been shown to be sensitive to change [29-31]. Secondary outcomes are self-reported disability, health-related quality of life and global perceived effect of treatment. The treatment efficacy variables will be measured at baseline and 10 weeks.

#### Specific outcome measures

• *Bothersomeness of back symptoms *measured by the Bothersomeness (0–10) Numerical Rating Scale [32].

• *Generic pain-related disability *measured with the Pain Disability Index [33].

• *Back-specific pain-related disability *measured with the Quebec Back Pain Disability Scale [34].

• *Patient-specific pain related disability *measured with the Patient Specific Functional Scale [35,36].

• *Health-related Quality of Life *measured with the SF-36v2 Health Survey [37].

• *Coping Strategies *measured with the Coping Strategies Questionnaire [38].

• *Global perceived effect of treatment *measured with the Global Perceived Effect Numerical Rating Scale (-5 to +5) [35,36].

#### Additional Measures for Supplementary Clinimetric Analyses

• Roland Morris Disability Questionnaire 24 item [39].

• Patient Specific Functional Scale version 2

#### Demographic Measures

• A demographic data sheet including; age, gender, height, weight; ethnicity, religion, marital status, smoking status, previous episodes of back pain, previous treatments for back pain, current treatments and current exercise activities will be completed at baseline assessment.

#### Usual Care Measures

• A bi-weekly list of the health services accessed by the participants in both control and intervention group will be collected via email.

#### Process Measures

• In-class attendance sheets (adherence to treatment)

• Class lesson-plan checklist (standardized instruction)

#### Data integrity

The integrity of trial data will be monitored by regularly scrutinizing data sheets for omissions and errors.

### Sample Size

We have designed the study to detect a clinically important difference of 1.5 units on the 0–10 bothersomeness scale (estimate for SD = 2.35), 1 unit on the 0–10 pain numerical rating scale (estimate for SD = 2), 1 unit on the 0–10 patient specific functional scale (estimate for SD = 1.8); 1 unit on the 0–10 Global Perceived Effect Scale (estimate for SD = 1.65), 4 units on the 24 item Roland Morris Disability Questionnaire (estimate for SD = 4.9). We have taken the SD estimates from trials that recruited a similar patient cohort [3,29,40]. Given these considerations we have chosen to design the study to detect an effect size of 0.5 SD. Based upon the results of a similar trial by our group [3] we have allowed for 15% non-compliance with treatment, 15% loss to follow-up, and assumed a correlation between baseline and change scores of outcomes of 0.5. Taking these factors into account with specifications of alpha = 0.05, power = 0.80 a sample size of 77 participants per group is required to detect an effect size of 0.50 SD [41]. Accordingly we will recruit 80 participants per group or 160 participants in total to allow for treatment in blocks of 8. Blocks of 8 allow us to randomize 4 subjects at the one time to the Tai Chi group and so have a sufficiently large class.

As a secondary analysis we will evaluate predictors of response to treatment. We estimate that it would require ~640 subjects to detect an interaction effect of the same magnitude as the main effect. We do not have the resources for such a study. Accordingly we acknowledge that we may miss an interaction effect in our analyses. Brookes and colleague's simulations demonstrate that when testing for effect modification, trials have the same power to detect an interaction effect that is twice the size of the main effect [42].

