### Randomization

#### Sequence generation and allocation concealment and implementation

The allocation sequence will be generated using the random number function in Excel. The allocation sequence will be generated by an investigator not involved in assessment and treatment codes placed sequentially into sealed opaque envelopes. Baseline assessment will be conducted prior to group allocation by an investigator blind to the allocation sequence. Following assessment, participants will be issued a sealed envelope containing their group allocation and those in tai chi group scheduled to attend their first class within one week.

The tai chi intervention includes a series of movements to be taught sequentially and is taught in a group format. For reasons of practicality, the randomization code was developed using a computer random number generator in a block size of 8. This allows us to allocate 4 subjects to the tai chi class, and 4 to control for each block. This assists scheduling of tai chi classes which are held in groups.

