### Statistical Methods

#### Primary analysis: treatment efficacy

Statistical analysis of primary and secondary outcomes will be based on the intention to treat principle. The effect of intervention on bothersomeness of pain, pain intensity, function, disability and global perceived effect will be determined using linear mixed models (random intercepts and fixed coefficients) which incorporate terms for treatment, time and the treatment by time interactions. The coefficients of the treatment by time interactions provided estimates of the effects of the tai chi intervention. A treatment effect size will be calculated for each of the follow-up time points and, if there is a statistically significant treatment effect at any time point, we will also calculate number needed to treat (NNT) to achieve pain recovery (pain < 1 out of 10: [43] and 95% confidence intervals.

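### Tai chi is taught in classes, but neither the planned model nor the sample size names a class effect; with any positive class correlation the standard error is somewhat too small

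*Protocol article*

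**What the plan says.** All references are to the Protocol article. Under *Study aim* and *Tai chi dosage and class format*, the intervention is 18 group sessions over 10 weeks. Home-practice barriers are discussed in class, and each group has its own attendance sheet. Under *Timeline*, controls continue usual care and may join a program only after follow-up.

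The block size was chosen with classes in mind. *Sample Size* says that blocks of 8 let the trial "randomize 4 subjects at the one time to the Tai Chi group and so have a sufficiently large class". The randomization section says: "This allows us to allocate 4 subjects to the tai chi class, and 4 to control for each block".

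*Primary analysis: treatment efficacy* specifies "linear mixed models (random intercepts and fixed coefficients"), with terms for treatment, time and treatment by time. The level of the intercepts is not named, and class, group and instructor do not appear.

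*Sample Size* states: "specifications of alpha = 0.05, power = 0.80 a sample size of 77 participants per group is required to detect an effect size of 0.50 SD". Its listed allowances are these: "we have allowed for 15% non-compliance with treatment, 15% loss to follow-up", and it "assumed a correlation between baseline and change scores of outcomes of 0.5". Recruitment is rounded up to 80 per group. The primary outcome's own target is "1.5 units on the 0–10 bothersomeness scale (estimate for SD = 2.35").

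**The concern.** Classmates start together, learn the same sequence of moves together and discuss practice together for up to 18 sessions. Their 10-week scores, which are unblinded self-reports, may therefore resemble one another more than scores from different classes do. Controls share no such experience, so the design is partially nested: clustered in one arm only.

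A participant intercept handles the correlation between one person's two measurements. It does nothing for correlation between classmates. If that correlation is positive and ignored, the confidence interval for the treatment effect is too narrow, the type I error exceeds 5% on every outcome analysed this way, and the real power is lower than the calculation implies.

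**Working it through.** **Inputs from *Sample Size* and the randomization section.** Alpha 0.05 (taken as two-sided), power 0.80, effect 0.5 SD, non-compliance 15%, loss 15%, correlation 0.5, 80 recruited per group, 4 tai chi participants per block.

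**Assumed.** Class ICC ρ = 0.01, 0.05 or 0.10 on the baseline-adjusted outcome, and one block per class, so m = 4 and there are 80/4 = 20 classes.

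**1. The plan's own figure.**
- Unadjusted: 2 × (1.960 + 0.842)² / 0.5² = 62.8 per group.
- Baseline correlation: × (1 − 0.5²) = 47.1.
- Dilution by non-compliance: / 0.85².
- Loss: / 0.85, giving 76.7, so 77.

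The stated allowances reach 77 on their own, so no class effect was included.

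**2. Effect of class.** The design effect in the tai chi arm is 1 + (m − 1)ρ, and in the control arm it is 1. The variance of the contrast is multiplied by f = [2 + (m − 1)ρ] / 2.
- True alpha = 2Φ(−1.96/√f).
- With 80 × 0.85 = 68 analysed per arm and a diluted effect of 0.5 × 0.85 = 0.425, power for a test that uses the correct standard error = Φ(0.425/√(2 × 0.75 × f / 68) − 1.96).
- Required n per group = 76.7 × f.

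| ρ (m = 4) | √f | True alpha | Power at 0.5 SD | n per group for 80% |
|---|---|---|---|---|
| 0 | 1.000 | 5.0% | 81.6% | 77 |
| 0.01 | 1.007 | 5.2% | 81.1% | 78 |
| 0.05 | 1.037 | 5.9% | 78.8% | 83 |
| 0.10 | 1.072 | 6.8% | 76.1% | 89 |

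**3. Break-even.** Setting power to 80% with 80 per group gives f = 1.043. Since f = 1 + 1.5ρ, ρ is about 0.029. The three extra participants per group absorb a class ICC up to that value.

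**4. The primary outcome's target.** 1.5/2.35 = 0.64 SD. Power with 80 per group is 95.5% at ρ = 0 and 92.6% at ρ = 0.10. By contrast, pain intensity (1/2 = 0.5 SD) sits exactly at the design target.

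**5. After loss.** With 15% loss, a class of 4 has a mean of 3.4 analysed members. Its effective size, allowing for unequal classes, is (3.4² + 4 × 0.85 × 0.15)/3.4 = 3.55. At ρ = 0.05 / 0.10 this gives alpha of about 5.7% / 6.5% and power of about 79.2% / 76.9%.

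**6. A cohort effect shared by the block.** Each block of 8 is split 4:4, so an effect common to the block cancels from the contrast. With cohort ICC ρ_b, f = [2 − 2ρ_b + (m − 1)ρ] / 2. For ρ = 0.05 and ρ_b = 0.05, f = 1.025 and alpha is about 5.3%. With ρ_b = 0.075, f = 1 and alpha is 5.0%.

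**The case against.** The size of the problem rests entirely on an ICC that the documents do not supply. There is reason to expect a small one: a standard teaching method, lesson plans with checklists, and apparently a single instructor. At ρ = 0.01 the stated 80% power is met. The level of the random intercepts is also unstated, and a condensed article may leave that to an analysis plan. All of this limits the size and certainty of the point. It does not remove it: the article lists its model terms and sample-size inputs, gives class no place in either, and 77 reproduces without it.

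Three stronger readings are tempting, and the documents do not support them.
- **Larger classes.** If two blocks were merged into classes of 8, ρ = 0.10 would give alpha of about 9.2% and power of 69% at 0.5 SD. But the article describes 4 participants per block going to the class and regards that as large enough. Merging is not stated.
- **An underpowered primary outcome.** The figures below 80% belong to the 0.5 SD design target, not to the 1.5-unit bothersomeness target.
- **Cohorts of 8 as further ignored clustering.** This points the other way. Because blocks are balanced, ignoring a shared cohort effect is conservative and partly offsets the class effect.

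**Conclusion.** The point holds in a limited form. One arm is clustered by design, and neither the stated analysis nor the sample size allows for it. For a positive class ICC and no offsetting cohort effect, the planned standard error is too small: by about 1% at ρ = 0.01 and 7% at ρ = 0.10 with classes of 4. The resulting excess in type I error is modest and applies to the primary outcome as well as the secondary ones. Whether power at 0.5 SD falls below the stated 80% depends on the ICC exceeding about 0.03. Primary-outcome power is not in doubt over the assumed range.

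The conclusion assumes participant-level intercepts, one block per class, and the article's own allowances for non-compliance, loss and baseline correlation. It calls for a correction to the analysis and the power statement. It does not invalidate the trial.

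**What to change.** - **Model.** Add a random effect for class in the tai chi arm only (a partially nested model), let the residual variance differ by arm, and use small-sample degrees of freedom such as Kenward-Roger. Add a term for randomisation block. Baseline precedes allocation, so the class effect must act on the 10-week measurement. A class intercept constant over both times would cancel from the treatment-by-time term and correct nothing.
- **Data.** Take class membership from the attendance sheets already kept.
- **Blinding of analysts.** Supply masked arm labels and class codes, with controls coded as singletons or the model specified in advance. The class structure itself can reveal which arm is which, so fixing the model beforehand is the safer protection. A single shared random effect on a block-by-arm code is not a substitute, because it gives controls class variance too.
- **Sample size text.** State an assumed ICC and class size, and give power for 160 participants as a range, without enlarging the trial.

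The cost is a change of wording, a slightly wider confidence interval and slightly lower stated power.
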